#### 2.8.2. Radiographic Evaluation of Caries Arrest of the Lesion

At the end of the 6th month, a digital radiograph evaluation of the surviving restoration will be done for comparison with the baseline radiograph. Radiographic evaluation will be done only at the end of the 6th month as it takes a minimum of 3–4 months for radiographic changes to be evident.

The digital radiographic evaluation of the restored teeth will be done by two independent blinded examiners. The efficacy of the treatment will be assessed by the presence or absence of an increasing radiolucent area below the restoration. Each radiograph will be classified using Ekstrand criteria [34].

### 2.9. Secondary Outcome

A questionnaire will be given to the participants after each visit to assess self-reported satisfaction and acceptability of the treatment. The discomfort of treatment experienced by the patient will be assessed using the facial scale of Wong–Baker [35].

### 2.10. Participation Timeline

Each eligible individual selected for the trial will be participating in the trial for a period of 6 months from their first visit (baseline). The participation timeline: (t_−1_ and t_0_) baseline visit [either first visit (t_−1_) for Enrolment and/or second visit (t_0_) for Allocation], (t_1_) revisit on the 7th day after intervention, (t_2_) revisit on the 30th day, and (t_3_) revisit at the end of 6th month (Table 1).

### 2.11. Sample Size

The sample size was determined by using the G*Power statistical analysis program. With an anticipated effect size of 0.4, the probability of alpha error of 0.05, and 80% power, the sample size is estimated to be 100 per group. Expecting a 10% attrition in the follow-up visit, the final sample size per group is 110. Therefore, the total sample size is 220.

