Atraumatic restorative treatment (ART) is a highly successful community-based approach for the treatment or secondary level of prevention of dental caries. It is an alternative approach for managing dental caries which involves the removal of infected tooth tissue using conventional hand instruments alone, without the use of anesthesia and rotary equipment. One of the indications for the pertinent use of ART concerned the elderly, particularly those who are impaired. The first such study on atraumatic restorative treatment was carried out amongst elderly subjects who were housebound due to psychiatric, physical, or psychological problems. After 1 year of placement, 79% of the ART restorations were considered successful [10]. In a two-year randomized controlled trial, ART presented the probability of survival rates of 84% compared to conventional techniques, consisting of the preparation of (the decayed) tooth using a rotary instrument (for removal of infected tissues) under local anesthesia, followed by resin-modified glass ionomer cement restoration [11]. When the effect of ART on adult patients’ comfort was assessed, it was noted that ART caused less anxiety than the traditional restorative methods using rotary instruments as the vibration and sound of the rotary instruments were absent [12].

ART is an important component of the Basic Package of Oral Care (BPOC) which also includes Affordable Fluoride Toothpaste (AFT), and Oral Urgent Treatment (OUT). This has been recommended by the WHO, and has been a successful community-based approach to reducing the burden of dental caries [13]_._ Considering the global rise of the elderly population with natural dentition in the coming decennium, a study covering the effectiveness of the ART approach, as part of a package of oral care for use among the adult population, should receive serious attention. However, the ART approach is not successful in some cases, especially in cavities that are less accessible through conventional hand instruments. Improper removal of caries lesions may lead to bacterial invasion, secondary caries, and failure of restoration [14].

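### The stated 80% power rests on an unlabelled effect size of 0.4 and is not tied to a difference in either primary outcome

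*Protocol article*

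**What the plan says.** Section 2.11 gives G*Power as the software and these inputs: "With an anticipated effect size of 0.4, the probability of alpha error of 0.05, and 80% power". From them it derives 100 per group, and then: "Expecting a 10% attrition in the follow-up visit, the final sample size per group is 110". The total is 220. The section does not say which outcome the 0.4 refers to, what kind of effect size it is, or which test was chosen.

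Section 2.8 lists two primary outcomes.

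- **Survival of the restoration** (2.8.1) is assessed at day 7, day 30 and month 6. Section 4 assigns it Kaplan–Meier curves, a log-rank test and Cox regression.
- **Radiographic caries arrest** (2.8.2) is read at month 6 in restorations that have survived, on this basis: "The efficacy of the treatment will be assessed by the presence or absence of an increasing radiolucent area below the restoration".

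Section 4 plans no t-test. The only ART rates in the article are background figures in the Introduction: "After 1 year of placement, 79% of the ART restorations were considered successful", and from a two-year trial, "ART presented the probability of survival rates of 84% compared to conventional techniques". Section 2.11 uses neither.

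**The concern.** A power figure means something only for a named outcome, a named test and a stated difference. Section 2.11 gives none of these. The effect size it uses returns the stated sample size most exactly under a comparison of means, which this trial does not make for either primary outcome.

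Readers of the eventual report will take a null result as coming from a trial with 80% power to detect something worthwhile. If the actual power for restoration survival is well below that, a null result could be misread as showing no benefit of adding SDF.

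**Working it through.** **Inputs from the protocol article.** Effect size 0.4, alpha 0.05, power 80%, 100 per group before attrition, 110 after (section 2.11); 1:1 allocation (2.1); 6 months of follow-up (2.10). Sidedness is not stated. Two-sided is assumed, because a one-sided t-test would give only 78 per group.

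**1. Reproducing the 100.**

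- Two-sample t-test, d = 0.4: the normal approximation is 2(1.960 + 0.842)²/0.4² = 98.1. The noncentral t gives 99.08, rounded up to 100, with power 80.4% at 100.
- Cohen's h = 0.4 for two proportions: 98.1, rounded up to 99.
- Chi-square w = 0.4: 50 in total. Risk difference of 0.4: 20–24 per group. Hazard ratio 0.4: 38 events (Schoenfeld). None of these fits.

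The t-test is the only reading tried that returns 100 exactly; h = 0.4 is one short.

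**2. What h = 0.4 would mean.** With h = 2·arcsin√p₂ − 2·arcsin√p₁ = 0.4, p₁ = 79% gives p₂ = 92.6%, and p₁ = 84% gives p₂ = 95.6%. For a pooled chi-square with n per arm,

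power = Φ{[|p₂ − p₁|√n − 1.96√(2p̄(1 − p̄))] / √[p₁(1 − p₁) + p₂(1 − p₂)]}.

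At n = 99 this is 78.5% and 77.3%.

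**3. Illustration for survival.** The assumptions are mine, not the protocol's: failures halved (chi-square) or hazard ratio 0.5 (log-rank), one restoration per person, 99 per arm, and 6-month ART success of 79%, 84% or 90%. The first two rates are borrowed from the 1-year and 2-year background figures; the third is assumed.

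Worked chi-square case, 79% against 89.5%: p̄ = 0.8425, so [0.105 × 9.950 − 1.96 × 0.5152]/0.5098 = 0.069, and Φ = 53%.

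For log-rank, SDF-arm survival is p₁^0.5, expected failures are 99[(1 − p₁) + (1 − p₁^0.5)], and power is Φ(½√d·|ln 0.5| − 1.96), where d is the number of failures.

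| Assumed ART success | Chi-square power | Expected failures | Log-rank power |
|---|---|---|---|
| 79% | 53% | 31.8 | 50% |
| 84% | 41% | 24.1 | 40% |
| 90% | 27% | 15.0 | 27% |

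Failures needed for 80% power at hazard ratio 0.5: 4(1.960 + 0.842)²/(ln 0.5)² = 65.3, so 66.

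**4. Illustration for arrest.** No control rate is given, so 50–70% is assumed. With 99 per arm, 80% power needs about 50% to 69% (19 points) or 70% to 86% (16 points).

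Section 2.8.2, however, reads arrest only in surviving restorations. If 79–84% of control restorations survived, about 99 × 0.79 = 78 to 99 × 0.84 = 83 control participants would be evaluable, again at one restoration each. With 78 in both arms, the detectable difference widens to about 22 points (from 50%) or 18 points (from 70%).

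**5. Attrition.** 110 × 0.9 = 99, not 100. Keeping 100 needs 100/0.9 = 111.1, so 112 per group. In the t-test calculation the slip moves power from 80.4% to 79.97%.

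**The case against.** Several stronger conclusions are tempting, and the documents do not carry them.

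- **That the calculation was a t-test, so the 80% belongs to neither outcome.** Section 2.11 never names a test. Under h = 0.4, rounding 99 up to 100 would be ordinary, and the 80% would then belong, nearly, to a binary comparison. What stands is that neither reading ties the figure to a stated rate or difference.
- **That the trial is underpowered.** The halving of failures and the 90% ART rate appear nowhere in the article. The 79% and 84% come from other populations and longer follow-up. Other inputs give other answers: at 100 per arm, 79% against 94% has 88% power by chi-square and 94% by log-rank.
- **That only 15–32 failures can be expected.** Section 2.4 admits people with more than one lesion, and section 4 plans tooth-level analysis. At an assumed 1.5 or 2 restorations per person, failures at 79% ART success rise to about 48 or 64, and log-rank power to 67% or 79%. These are upper bounds, because clustering is ignored.
- **That the type I error is 9.75%.** 1 − 0.95² = 0.0975 requires independent outcomes and success on either one. Section 2.8.1 defines arrest beneath an intact restoration, so the two outcomes are linked.
- **That the attrition slip matters.** Its effect is negligible.

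It is also fair to say that a condensed article may leave the test and control rate to a fuller document. But the article does publish a power figure, and the objection is to that sentence: as it stands, a reader cannot connect the 80% to either declared primary outcome.

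**Conclusion.** The point holds in this form: section 2.11 claims 80% power at an effect size whose scale, outcome and test are not given. The sample size reproduces exactly as a comparison of means and within one participant as h = 0.4. Both primary outcomes are binary or time-to-event, so the claim is not tied to a difference in either. Under the more favourable reading, h = 0.4, the implied effect would remove roughly two-thirds to three-quarters of failures at the cited ART rates (21% to 7.4%, and 16% to 4.4%), and the article neither states nor justifies such an effect.

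The exact power cannot be given, because no planning rate or hazard ratio is stated. The illustrative 27–53% for survival and the 16–19 points for arrest rest wholly on the assumptions listed with them. They show how far the true figure could lie from 80%, not what it is.

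**What to change.** Keep N = 220 and rewrite section 2.11.

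- Replace the unlabelled effect size with the outcome and test that the calculation serves, the assumed ART proportion with its source, and the difference detectable with 80% power.
- For arrest, base this on the number expected to be evaluable after both attrition and loss of restorations. That number is below 99 per arm.
- For survival, state the expected failures and the power they give, with the assumed number of restorations per person and the allowance for clustering. Do not claim 80% unless that calculation supports it.
- Say which primary outcome the 0.05 is spent on, or how it is shared. Which to choose is the investigators' design decision.
- Correct the attrition line: 110 per group less 10% leaves 99.

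This changes wording only and adds no participants. The cost is that the stated power becomes less favourable.

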According to the socioeconomic census in India in 2011, 68% of the population is still living in rural areas [31] where the possibility of health systems integrating to their fullest extent is still a difficult task. Therefore, easily accessible and less expensive treatments should be promoted for changing the population’s attitude towards dentistry, although India has been advancing in various aspects of oral health [32]. Educating on new concepts that can be easily perceived and applicable through community health workers and dental auxiliaries in society can bring about a drastic change in this prejudice about dental well-being. With the advancement of community-based procedures such as atraumatic restorative treatment and silver diamine fluoride application more attention can be bought to the population towards dental care and its importance.

A combination of SDF application and ART together would be an innovative, minimally invasive method that imparts both bactericidal effects leading to caries arrest and restores the function of the tooth. Thus, we would be able to better address the drawbacks of both these procedures when applied individually. Such a combination of 38% silver diamine fluoride application along with atraumatic restorative treatment on the cavitated carious lesion of permanent teeth in adults has not been reported in the literature. If found successful, this would be an extremely valuable technique that will be of great advantage for oral health in community-based projects.

The objective of the clinical trial is to compare the effect of the application of 38% SDF along with atraumatic restorative treatment, against atraumatic restorative treatment alone, in arresting active occlusal carious lesions on permanent teeth. It also intends to compare the survival of the restoration. The trial also assesses the patient satisfaction and acceptability of the application of the SDF.

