## 2. Methods

### 2.1. Study Design

This is a randomized, controlled trial with two parallel comparator arms, having a 1:1 allocation ratio (Figure 1).

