### 2.8. Primary Outcomes

#### 2.8.1. Assessment of Survival of the Restoration 

The follow-up will be conducted on the 7th and 30th days, and the end of the 6th month to evaluate the survival of the restoration (Table 1).

Each restoration will be assessed according to codes and criteria used in ART studies as proposed by Jo E Frencken [13]. Cavities treated with SDF and ART will be considered arrested caries lesions when the tooth surfaces with active caries at baseline visit change into surfaces with arrested caries beneath an intact restoration. The restored tooth is asymptomatic and clinically functional.

In the SDF and ART or ART-treated tooth, if caries progress beyond the dentine, it will be considered not arrested. In such conditions, the patients will be advised to follow standard treatment protocols. During the follow-up period, if the restored tooth is extracted due to infection, trauma, or fracture, the concerned tooth will not be included in the study.

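### Two unranked primary outcomes share one unsplit alpha of 0.05 with no stated success rule, so the overall error exceeds 0.05 if either outcome may carry the claim

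*Protocol article*

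**What the plan says.** - **Two primary outcomes.** Section 2.8 is headed "Primary Outcomes". Section 2.8.1 covers survival of the restoration at day 7, day 30 and month 6. Section 2.8.2 is headed "Radiographic Evaluation of Caries Arrest of the Lesion" and describes a month 6 reading against the baseline radiograph. Neither is placed above the other.
- **One sample size.** Section 2.11 starts "With an anticipated effect size of 0.4" and continues with "the probability of alpha error of 0.05, and 80% power, the sample size is estimated to be 100 per group". It then adds 10% for attrition to reach 110 per group, 220 in total. No outcome, type of test or sidedness is attached to the 0.4.
- **Both compared.** Section 4 plans between-arm comparisons of arrest and of survival at the study visits. It gives no significance level per test, no order and no success rule.
- **A hint of priority.** The title speaks of arresting caries. The objective in section 1 puts arrest first and then adds "It also intends to compare the survival of the restoration". Section 2.8 lists them the other way round.

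**The concern.** The 0.05 in section 2.11 is the error rate of a single comparison. With two primary outcomes and no rule linking them, a significant result on either could be reported as a positive primary finding. The 0.05 would then not describe the trial's chance of a false primary claim.

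The missing rule also leaves the sample size exposed. If alpha is later split, the 80% power no longer holds at 100 per group. If both outcomes are later required, the power to win on both is in general below the power of either one. A rule chosen after results are known would carry little weight.

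**Working it through.** **Inputs.** From section 2.11: alpha 0.05, power 80%, effect size 0.4, 100 per group. From section 2.1: two parallel arms "having a 1:1 allocation ratio". Assumptions, because the article does not state them: the 0.4 is a standardised difference between two means, the test is two-sided, and each primary outcome contributes one test.

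**1. Reproduce the plan's figure.** Normal approximation: n per group = 2 × ((1.960 + 0.842)/0.4)² = 98.1, so 99. The two-sample t-test solution is 99.08, so 100 per group, with power 80.4% at n = 100. A one-sided test at 0.05 needs only 78. The stated 100 therefore matches one two-sided test that uses the whole 0.05.

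**2. Overall error if either outcome may support the claim, each at two-sided 0.05.**

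Independent tests: 1 − 0.95² = 0.0975.

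Correlated tests: 1 − P(|Z₁| < 1.96 and |Z₂| < 1.96), with Z₁ and Z₂ bivariate normal with correlation ρ. The article gives no correlation, so ρ is an assumed range.

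| ρ | At least one false-positive result, either direction | At least one false result favouring the combination |
|---|---|---|
| 0 | 9.75% | 4.9% |
| 0.3 | 9.5% | 4.8% |
| 0.5 | 9.1% | 4.5% |
| 0.7 | 8.3% | 4.2% |
| 0.9 | 7.0% | 3.5% |
| one test only | 5.0% | 2.5% |

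The last column is 1 − P(Z₁ < 1.96 and Z₂ < 1.96); at ρ = 0 it is 1 − 0.975² = 0.0494.

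**3. Overall error under other rules.**
- Both must succeed: at most 0.05. Joint power, if both effects were 0.4 and the tests independent, would be 0.804 × 0.804 = 0.646, and higher with positive correlation.
- Fixed order, second test only if the first is significant: at most 0.05, no split needed.
- Bonferroni, 0.025 each: 1 − 0.975² = 0.0494 if independent. Power at 100 per group falls from 80.4% to 71.5% (t-test), and 121 per group are needed for 80%. These power figures carry the two-means assumption.

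**4. Are the outcomes independent?** Not by design. Section 2.8.1 defines arrest under an intact restoration, and section 2.8.2 reads the radiograph only where the restoration has survived. So 9.75% is an upper bound, and the true figure probably lies lower, by an amount the article does not allow one to compute.

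**The case against.** The strongest reply is that levels per test, test order and the success rule are commonly left to a full protocol or an analysis plan, and neither is shown. That stands for the mechanics of adjustment. It does not cover which outcome is primary or which outcome the sample size serves. Those are design statements, and the article makes them: two unranked primary outcomes, paired with a calculation for one test.

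A reader might infer that each outcome is tested at 0.05, that a win on either is enough, and that the error rate therefore nearly doubles. The article does not say this. Its only alpha is in section 2.11, and it states no success rule. Nearly double also requires independent tests, whereas these outcomes are linked.

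A reader might also infer that a trial declared in favour of the combination would be wrong nearly 10% of the time. That mixes two quantities. The 9.75% counts errors in both directions; false results favouring the combination reach at most 4.9%, against 2.5% for one test.

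Finally, it can be said that making arrest the first test is a preference, since section 2.8 lists survival first. This stands in part. The title and objective point to arrest, but the investigators must make the choice, and arrest has the drawback of being read only in surviving restorations.

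**Conclusion.** The point holds in conditional form. If either primary outcome may support the claim at two-sided 0.05, the overall error is above 0.05: at most 9.75%, and about 7.0% to 9.5% for assumed correlations of 0.9 down to 0.3. If both must succeed there is no inflation. The article does not say which rule applies.

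This affects what a positive result would mean; it does not invalidate the trial. It should be settled before outcomes are seen.

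One further inference should be resisted: that ordering the tests would also confirm the sample size. The 0.4 is tied to no outcome and reproduces as a comparison of two means. Arrest is a present-or-absent reading in surviving restorations, possibly fewer than 100 per group. Nothing in the article shows that 100 per group gives 80% power for it.

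**What to change.** 1. In sections 2.8 and 4, state a fixed test order before outcomes are seen. Put caries arrest at month 6 first, as the title and objective imply. Test restoration survival at two-sided 0.05 only if arrest is significant. Specify one confirmatory test for each outcome, so that the comparisons at earlier visits are supportive.
2. In section 2.11, name the outcome, the test and the sidedness to which the 0.4 and the 80% power refer. If it is arrest, express the assumption as proportions in each arm and allow for restorations that do not survive to be read.

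**Cost.** The first change takes about one sentence in each section and no more participants, and it holds the overall alpha at 0.05. The small downside is that survival cannot be claimed as confirmatory if arrest is not significant. The second change is also a wording change, but it may show that the power for arrest differs from 80%.

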### 2.12. Study Implementation

The adult patients visiting for routine dental care to dental school will be recruited for the study. A clinical examination will be carried out on prospective participants. If the individual satisfies the inclusion criteria, the participant will be informed of the options for caries prevention by ART ± SDF. If they agree, they would be offered the choice of participation in the trial and the consenting process will be followed. The patient screening will continue till the target population is attained (n = 220).

Enrolment of the study population will be done over 24 months and follow-up visits are expected to be completed at the end of the 30th month, which will be followed by analysis and report writing. The total study duration is of three years.

The selected participants for the trial will be randomly allocated to a study arm, as per computer-generated randomization. The randomization code will not be revealed to the principal investigator until the participant has been recruited into the clinical trial after all the baseline assessments are complete. This is to ensure allocation concealment. Opaque-sealed envelopes containing randomization codes, in compliance with the randomization list, will be employed for allocation concealment. The randomization will be conducted by the research assistant. The randomization list will remain with the trial coordinator for the whole duration of the research. Due to the apparent nature of the treatment involved, neither the study participant nor the principal investigator (PI) can be blinded.

The PI will be trained for the study requirements, standardized in the assessment of the coronal carious lesion, caries cessation, 38% SDF application and ART, or ART alone, eliciting the required details from the study subjects in a consistent replicable method, and counseling for compliance. The procedure to be conducted and the data to be collected at each study visit will be inspected in detail. During the training sessions, details about procuring and entering the quality data in the clinical record forms will also be discussed. Calibration of PI (AV) will be done before and during the study by another clinical expert (CJ) and reliability will be expressed using Cohen’s kappa statistic.

Once an individual is enrolled in the trial, an appropriate effort will be taken to follow the study participant for the entire study period of six months. Each patient will have the right to withdraw from the trial at any time. If it is due to an adverse event, review visits will be arranged by the PI until the adverse event has been resolved. There will be no restrictions in case the trial participant requires any dental treatments other than that of the concerned tooth.

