Glass ionomer cement (Glass Ionomer High Strength Posterior restorative, GC Corporation, Tokyo, Japan) will be prepared according to the manufacturer’s instructions. The restorative material will be placed into the prepared cavity using a plastic filling instrument. The press finger technique will be used for approximately one minute and the restoration will be coated with petroleum jelly. A carver would be used to remove the excess material. The height of restoration will be adjusted after the bite is checked using articulation paper. A photograph and a digital radiograph of the restored tooth will be taken after the procedure and at the end of the study.

*Procedure to be followed for study arm 2:*

*Placement of ART restoration*

A preoperative photograph of the selected tooth will be taken. The preparation of the cavity will be done as stated above using hand instruments. Conditioning of the prepared tooth surface will be done with an applicator tip saturated with the polyacrylic acid liquid for 10–15 s. Glass ionomer cement (GIC Fuji IX, G C CORPORATION, [name]) will be prepared according to the manufacturer’s instructions and placed into the cavity using a plastic filling instrument. The press finger technique will be followed, and the surface of the restoration will be coated with petroleum jelly. The bite will be checked using articulation paper and the occlusal adjustments will be done. A photograph and a digital radiograph of the restored tooth will be taken after the procedure and at the end of the study.

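### No blinded assessment of restoration survival, a primary outcome, is stated, and the text points to the unblinded principal investigator as its assessor

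*Protocol article*

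**What the plan says.** All references are to the Protocol article.

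- **Outcome.** Section 2.8.1 lists restoration survival first under the primary outcomes, with assessments on days 7 and 30 and at the end of month 6. On scoring it says: "Each restoration will be assessed according to codes and criteria used in ART studies". The sentence is passive and names no assessor.
- **Blinding of people.** Section 2.12: "neither the study participant nor the principal investigator (PI) can be blinded".
- **Training.** Section 2.12 has the principal investigator "standardized in the assessment of the coronal carious lesion, caries cessation, 38% SDF application and ART, or ART alone". Eliciting participant details and completing the record forms belong to the same training.
- **Calibration.** Section 2.12 says that calibration of the principal investigator "will be done before and during the study by another clinical expert", summarised by Cohen's kappa.
- **Follow-up contact.** Section 2.14 has the principal investigator carry out an oral examination at each planned visit, for adverse events.
- **Blinded reading.** Section 2.8.2: "The digital radiographic evaluation of the restored teeth will be done by two independent blinded examiners". The 6-month radiographic evaluation is confined to restorations that survive.
- **Images.** Section 2.7, for both arms: "A photograph and a digital radiograph of the restored tooth will be taken after the procedure and at the end of the study". No photograph is mentioned for day 7 or day 30.
- **Analysis.** Section 4 plans Kaplan–Meier curves with a log-rank test for survival.

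**The concern.** The article deals with blinding directly. It provides blinded readers for one primary outcome and says nothing of the kind for the other. Coding a restoration against ART criteria calls for judgement at the margin between acceptable and failed. An assessor who knows the arm, and may have placed the restoration, can lean one way in borderline cases without intending to.

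The effect would not stop at survival. Section 2.8.1 ties arrest to an intact restoration, and 2.8.2 passes only surviving restorations to the radiograph readers. An arm-related tilt in the survival score would therefore also select, differently by arm, the teeth on which arrest is judged. Blinding the readers does not repair that selection. Nor does kappa: two assessors who both know the arm can agree well and share the same leaning.

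**Working it through.** **1. Who scores survival?** Set side by side, the sections give:

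| Question | Section | Answer in the text |
|---|---|---|
| Who applies the ART codes? | 2.8.1 | Not stated |
| Who is trained and calibrated for clinical assessment? | 2.12 | The principal investigator |
| Does that training list name restoration survival? | 2.12 | No: it names the carious lesion, caries cessation and the two treatments |
| Who examines the mouth at each visit? | 2.14 | The principal investigator, for adverse events |
| Is any other clinical assessor named for follow-up? | – | No; the second expert appears only for calibration |
| What do the blinded examiners read? | 2.8.2 | Radiographs only |

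The principal investigator as survival assessor is thus a strong inference, not a stated fact. That no blinded assessment of survival is stated follows from the text directly.

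**2. The plan's own figure.** Section 2.11 gives effect size 0.4, alpha 0.05 and power 80%. Two-sided, n per group = 2 × ((1.960 + 0.842)/0.4)² = 98.1, so 99; the t-test version gives 99.08, so 100. The stated 100 reproduces. With attrition, 100 × 1.10 = 110 as stated (100/0.90 gives 112). Nothing here depends on who scores the outcome, so blinding would not alter the sample size. The 100 per arm is used below.

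**3. What a tilt in scoring would do (illustration).**

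Inputs:
- n = 100 per arm, from 2.11.
- True survival 84% in both arms. This is an assumption, borrowed from the two-year ART figure in the Introduction.
- Scored survival raised by t points in one arm only. This is an assumption; the protocol gives no value.
- Two-sided 5% test of two proportions, as a simple stand-in for the planned log-rank test.

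With p₁ = 0.84 + t, p₂ = 0.84 and p̄ their mean:

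- SE₀ = √(2p̄(1 − p̄)/n)
- SE₁ = √((p₁(1 − p₁) + p₂(1 − p₂))/n)
- P(reject) = Φ((t − 1.96·SE₀)/SE₁) + Φ((−t − 1.96·SE₀)/SE₁)

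*t = 0.02:* SE₀ = 0.0505, SE₁ = 0.0505; P = 0.059 + 0.009 = 0.068.

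*t = 0.05:* SE₀ = 0.0483, SE₁ = 0.0482; P = 0.177 + 0.001 = 0.178.

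From 79%, the one-year ART figure in the same part of the Introduction, the results are 0.064 and 0.148.

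**4. How large are these tilts?** At 84% survival, 16 of 100 restorations fail. If the tilt comes from passing true failures in one arm, 2 points means 2/16 = 12.5% of them and 5 points means 5/16 = 31%.

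**The case against.** Four points deserve weight.

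*The assessor is not named.* A reader might infer that the protocol has the principal investigator score survival. It does not say so. Section 2.8.1 is silent, the training list omits survival, and the visit examination in 2.14 is for adverse events. A condensed article may leave the chairside assessor to the full protocol. This stands against any flat statement that the investigator scores survival. It does not remove the gap: the article describes blinding for one primary outcome and none for the other.

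*The illustration can be pushed too far.* An 8-point tilt gives a rejection probability of about 41%, and it is tempting to lead with that. But 8/16 means passing half of all true failures in one arm, which is not leniency in borderline cases. The 84% is a two-year figure, whereas this trial ends at 6 months, and the planned test is a log-rank test. The figures show direction and rough size; they do not measure this trial's bias.

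*A photograph score should not replace the primary measure.* Photographs are planned only after the procedure and at the end of the study, so they cannot supply events on days 7 and 30. A single binary reading would displace the time-to-event analysis in section 4. Nothing in the documents shows that ART codes can be graded from a photograph, and staining may disclose the arm despite the potassium iodide step in 2.7. This stands, and limits the blinded score to a supporting role.

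*Part of the problem is already handled.* The protocol explains why operator and participant cannot be blinded, calibrates the investigator against a second expert, and has arrest read blind on radiographs. That is fair, but the blinded reading starts only after the survival score has selected the teeth.

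**Conclusion.** The point holds in a limited form. The protocol states no blinded assessment of a primary outcome and points, without saying so, to the unblinded principal investigator as its assessor. Because radiographs are evaluated only for surviving restorations, the same score conditions the other primary outcome.

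The size is not known. On the assumed values, a small tilt does little (5% to about 7%) and a moderate one matters (about 18%, or about 15% from 79% survival). The recommendation does not depend on either figure: it rests on the contrast between 2.8.1 and 2.8.2 and on the low cost of closing it. The documents do not support a claim that the survival result will be biased. This is a change that should be made, not a fault that invalidates the design.

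**What to change.** 1. In 2.8.1 and 2.12, name who scores restoration survival at each visit and whether that person treated the patient or knows the arm.
2. Have the two blinded examiners also score the coded 6-month photograph together with its radiograph as restoration present or failed, without sight of the arm, pre-operative images or operator notes.
3. Keep the chairside ART codes on days 7 and 30 and at month 6 for the Kaplan–Meier and log-rank analysis.
4. In section 4, prespecify the blinded 6-month score as a key sensitivity analysis. Report its agreement with the chairside code separately by arm, and treat a survival difference as robust only if the blinded score points the same way.
5. In 2.8.2, have the 6-month radiograph read for every retained tooth, not only for those the chairside score calls surviving. Section 2.7 already plans that image for restored teeth in both arms.

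**Cost.** A few minutes of extra reading per tooth, by examiners already engaged and on images already planned; no change in sample size. Limits remain: residual stain may reveal the arm in some photographs, small marginal defects are harder to grade than at the chair, and days 7 and 30 stay unblinded.
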